## Methods

### Informed consent and ethical considerations

The study was approved by the Ethics Committee of the IRCCS Fondazione Don Carlo Gnocchi. The Study was registered at ClinicalTrials.gov, ID: NCT02499653. Amendments will be submitted to both the Ethics Committee and the Clinical Trials Register. All subjects will provide written, informed consent before the study begins. In particular, a psychologist will discuss the trial with patients in light of the information provided in the Consent Form and in Information Sheets. Patients will then be able to have an informed discussion with the participating consultant. The psychologist will obtain written consent from patients who are willing to participate in the trial.

All study-related information will be stored securely at the study site. All participant information will be stored in locked file cabinets in areas with limited access at Fondazione Don Carlo Gnocchi, Milan. All laboratory specimens, reports, data collection, process and administrative forms will be identified by a coded ID (identification) number only to maintain participant confidentiality. All records that contain names or other personal identifiers, such as Locator Forms and Informed Consent Forms, will be stored separately from study records identified by code number. All local databases will be secured with password-protected access systems. Participants’ study information will not be released outside of the study without the written permission of the participants. Moreover, the principal investigators will be the only persons allowed direct access to the data sets, and will also have access to other sites’ data by request. To ensure confidentiality, data dispersed to project team members will be blinded of any identifying participant information.

### Subjects and setting

The study will be conducted in a Clinical and Research Centre, HD Respiratory Rehabilitation Unit, Fondazione Don Carlo Gnocchi, IRCCS Santa Maria Nascente, Milan (Italy), a centre chosen based on documentation of, among other things, patient availability.

We aim to recruit 150 patients with COPD who have been recommended to use NIV based on the GOLD criteria (from moderate to severe) [36, 37].

The *inclusion criteria* are as follows: age 18 years or older; inpatients or outpatients; with moderate (GOLD 2–50% ≤ FEV_1_ < 80% predicted) to severe (GOLD 3–30% ≤ FEV_1_ < 50% predicted) COPD.

The *exclusion criteria* are as follows: refusal of consent; pregnancy; oncological history or history of psychiatric/mental disorders, according to *Diagnostic and Statistical Manual of Mental Disorders, fifth edition* (DSM-V) criteria [38, 39], with the exception of anxiety and depression, as indicated in the patient’s clinical record; immunosuppressive disease as the principal condition; stable use of antidepressant drugs.

### Design and interventions

This study is a randomised control trial (RCT) (for the flowchart of the study design, see Fig. 1).

**Fig. 1 Fig1:**
[figure not shown]
Flowchart of the study design

Subjects in the *experimental group* will receive a brief psychological intervention in addition to standard. This will include counselling and psychological support, mindfulness-based cognitive restructuring exercises [40] and relaxation training [41]. The intervention will also include neuropsychological rehabilitation exercises if required; this will be decided on a case-by-case basis, using clinical notes and the Addenbrooke’s Cognitive Examination (ACE-R) and Confusion Assessment Method (CAM) scores. Each patient’s psychological needs will be assessed at the beginning of the psychological intervention, paying special attention to aspects related to the disease (e.g. perception, understanding, awareness of symptoms). Thereafter, the psychological intervention will give more importance to the risks, doubts and fears arising from use of NIV. The intervention will consist of cognitive reframing exercises, relaxation training and, if necessary, neuropsychological rehabilitation exercises. Specifically, these intervention components extend from lowering arousal to providing disease information and management in order to understand better how to cope with NIV and with COPD symptoms, to an emotionally supportive environment in which subjects can address their fears and anxieties, as well as behavioural and cognitive coping strategies. The duration of the intervention will vary from a minimum of four weekly sessions to a maximum of eight according to the needs of the patient. Each session will last about 30–45 min. Sessions will be conducted in a hospital setting, or at the patients’ house or via telemedicine if patients are unable to attend the hospital.

Subjects assigned to the *control group* will spend six sessions watching videos related to the management of their disease (sessions will last about 30 min).

The psychologists who conduct the intervention will be blind to the assessments and vice versa (for the study procedure: schedule of enrolment, interventions and assessments, which reflects the Standard Protocol Items: Recommendations for Interventional Trials (SPIRIT) figure, see Fig. 2).

**Fig. 2 Fig2:**
[figure not shown]
Study procedure: schedule of enrolment, interventions and assessments, reflecting the Standard Protocol Items: Recommendations for Interventional Trials (SPIRIT) figure

### Sample size

Based on statistical analysis, preventive inherent power and sample size [40] we anticipate that the study will require 150 subjects. We will recruit between 128 subjects (statistical power of 0.80; *α* = 0.05; 1 − *β* = 0.80; *t* (126) =1.97) and 172 subjects (statistical power equal to 0.90; *α* = 0.05; 1 − *β* = 0.90; *t* (170) = 1.97). The inherent power also emphasises that such analyses have been carried out using data for a scientific study that have a comparable primary outcome [33].

### Randomisation

#### Sequence generation

The patients will be randomised through a simple method, extracting a unit from the population using a method which guarantees the causality of the extractions (https://www.random.org).

#### Allocation concealment and implementation

Randomisation will be implemented using a computer system and the sequence will be concealed using a centralised service, since this cannot be subverted by either investigators or assessors and provides independent verification preventing the investigators to know the allocation sequence in advance until subjects are assigned to groups. We will calculate the dropout rate for both groups.

### Blinding (masking)

Subjects will not know in advance to which group they will be assigned and that the kind of treatment between control and experimental groups is different. Assessors will be blind to group allocation. A debriefing will be provided at the end of the study: the psychologist who carried out the intervention will debrief with the patients and will send them a report about the study’s findings.

### Assessment

#### Sociodemographic variables

At the first assessment we will collect sociodemographic information (age, gender, weight, height, level of education, current job and/or previous employment, cohabitation, smoking and alcohol consumption, current and historical levels of physical activity, duration of disease, drug therapies for respiratory disease, use of psychotropic drugs, number of hospital admissions during the last year, exacerbations and comorbidities).

#### Medical and clinical assessment

This will cover:NIV use (prescribed hours, effective hours and their difference)The effects on change from baseline in acceptance of NIV in COPD patients as measured by weekly means and standard deviations of hours of use of NIV as recorded by the ventilatorChanges in adherence defined as the difference between prescribed and effective NIV hoursSurvival rate at different time after starting the adaptation to NIV, reported in terms of monthsSimple spirometry: forced expiratory volume in the first second (FEV1); forced vital capacity (FVC); FEV1/FVCFatigue, measured by the Fatigue Severity Scale (FSS) [42]Emogasanalysis (EGA): potential of hydrogen (pH); partial pressure of oxygen in arterial blood (PaO2); partial pressure of carbon dioxide in arterial blood (PaCO2); hydrogen carbonate concentration (HCO3)

#### Psychological assessment

##### Anxiety and depression

Anxiety and depression will be assessed using the 14-item Hospital Anxiety and Depression Scale (HADS) [43]. Responses refer to the previous week and are given using a four-point Likert scale. The scale is designed to assess the severity of anxiety and depression simultaneously; it is organised into two 7-item subscales, HADS-A and HADS-D, which generate separate subscores for anxiety and depression, respectively.

##### Quality of life

QoL will be assessed using the EuroQoL (EQ-5D) [44, 45], a short, simple questionnaire consisting of two sections. The first comprises five health-related items (covering mobility, self-care, usual activities, pain/discomfort, anxiety/depression), and is used to assess the severity of health problems. The second section comprises a Visual Analogue Scale – a representation of a thermometer with graduated markings which respondents use to indicate their perception of their current health status (0 = ‘worst possible health state’ to 100 = ‘best possible health state’).

##### Representation of the disease

The representation that the patient has of their disease will be assessed using the Brief Illness Perception Questionnaire (BIPQ), developed by Broadbent and colleagues [46, 47]. This can be viewed as a practical application of the theory of self-regulation. Items can be organised into three categories: (1) identity of the disease (14 items), (2) opinion of the disease (38 items) and (3) causes of the disease (18 items). Responses are given using a five-point Likert scale (1 = ‘strongly disagree’ to 5 = ‘strongly agree’).

##### Representation of proposed therapies

This assessment will be based on a modified version of the Beliefs about Medicines Questionnaire (BMQ) developed by Horne and colleagues [48]. This tool is used to assess patients’ beliefs about medication. It consists of two scales: Specific Beliefs and General Beliefs. We will use a modified version of the BMQ designed to capture beliefs about NIV.

##### Therapeutic compliance

This will be assessed using the Questionario sull’Adesione alla Terapia Farmacologica e Dietetica (QAF) [49]. The QAF consists of 19 items to which responses are given using a four-point Likert scale (1 = ‘this is always true of me’; 2 = ‘this is often true of me’; 3 = ‘this is almost never true of me’; 4 = ‘this is never true of me’). Some of the items in this questionnaire are modifications of items of the Medication Adherence Rating Scale (MARS) which is used in psychiatry to assess adherence to drug therapy. The items were compiled and assorted randomly through extraction.

##### Self-esteem

Self-esteem will be assessed with the 10-item Rosenberg Self-Esteem Scale (RSES) [50]; responses are given on a four-point Likert scale (1 = ‘strongly agree’ to 4 = ‘strongly disagree’). The scale provides an indication of overall self-esteem and sense of self-worth.

#### Cognitive assessment

##### Addenbrooke’s Cognitive Examination (ACE-R)

The ACE-R [51] is a brief cognitive test that assesses five aspects of cognition: attention/orientation (AO), memory (M), verbal fluency (F), language (L) and visuospatial abilities (VS). Administration of the ACE-R takes 15 min on average.

##### Confusion Assessment Method (CAM)

This tool will enable us to evaluate features considered to be of great diagnostic importance, namely: acute onset, attentional deficits, disorganisation of thought, altered level of consciousness, disorientation, memory deficits, disorders of perception, psychomotor agitation, psychomotor retardation and disturbance of the sleep-wake cycle [52].

#### Econometric assessment

We will analyse the direct (e.g. supply of equipment, maintenance tasks, etc.) and indirect (e.g. cost of hospitalisation for relapse, additional care, indirect social costs, etc.) costs of the management of COPD in our sample, referring to clinical notes and medical files. Changes in QoL and life expectancy data will be used to estimate QALYs [53, 54] and DALYs [55] and, by comparing our data with international norms, we will gain insight into the sustainability and cost-efficiency of the psychological intervention. We also plan to use econometric tools such as the Work Productivity and Activity Impairment Questionnaire – Respiratory Symptoms (WPAI-RS) [56, 57].

The medical assessment will take about 30 min and the psychological assessment about 45–50 min. The order of administration of the questionnaires and tests will be randomised on a per subject basis.

Finally, semistructured interviews (qualitative data) will be carried out to provide insight into subjects’ views on use of the NIV equipment.

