**Methods:**

A two-arm randomised controlled trial will be conducted. We aim to recruit 150 COPD patients for whom NIV is indicated. The experimental group will receive a brief course of psychological support that will include counselling, relaxation and mindfulness-based exercises. In some cases, it will also include neuropsychological rehabilitation exercises. Support will be delivered via four to eight meetings at the HD Respiratory Rehabilitation Unit, at home or via telemedicine. Controls will receive standard care and watch educational videos related to the management of their disease.

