### Objectives

The primary objective of the study is to evaluate the effects of psychological support on the acceptance of, and adherence to, NIV. Secondary aims include assessment of the change in QoL between baseline and after 3, 6 and 12 months following recruitment, identification of psychological and clinical factors that predict rejection or misuse of NIV, and factors that predict the success of the psychological intervention.

The primary outcome will be a latent variable related to indices of use of NIV equipment and adherence to treatment regime: the effects on change from baseline in acceptance to NIV in COPD patients at 3, 6 and 12 months as measured by weekly means and standard deviations of hours of use of NIV as recorded by the ventilator and changes in adherence defined as the difference between prescribed and effective NIV hours. Change in QoL will also be measured relative to baseline at 3, 6 and 12 months using the EuroQoL (EQ-5D) questionnaire, respiratory, functional and biomedical parameters. Survival rates after starting the adaptation to NIV and psychological variables will be considered as secondary outcomes.

As well as evaluating clinical and psychological variables we will also evaluate econometric outcomes. The study will explore the potential impact of the psychological intervention on the cost to the Italian welfare system of providing health care for patients with COPD. These assessments will be based on standard econometric indices (e.g. quality-adjusted life years (QALYs); DALYs).

Finally, semistructured interviews will be conducted to gain insight into patients’ perceptions of NIV.

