### Proposed analyses

Descriptive analyses will be performed for all study variables. We will assess the effect of the interaction between treatment (experimental versus control) and time (three repeated measures) on primary outcome variables (acceptance of treatment; adherence to treatment). Missing data will be imputed with multiple imputation techniques [58, 59].

Before-after differences will be analysed with appropriate within-group tests (paired samples *t* test; Wilcoxon test). Multiple regression will be used to assess the influence of baseline variables on outcome indicators and identify predictor variables.

The analysis will be performed using the intention-to-treat procedure. The significance level will be 5% (*p* ≤ 0.05). Data analysis will be performed using SPSS software.

Data collection and analysis will begin in month 1 and will last for 24 months, i.e. until 1 month after the last follow-up data have been collected.

We will report reasons for withdrawal for each randomisation group and compare the reasons qualitatively. The effect that any missing data might have on results will be assessed via sensitivity analysis of augmented data sets. Dropouts (essentially, participants who withdraw consent for continued follow-up) will be included in the analysis by modern imputation methods for missing data.

For more details about the trial, refer to the SPIRIT Checklist (Additional file 1).

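### The only comparison stated for the intervention's cost-efficiency is with international norms, which cannot isolate its effect although a randomised control arm is available

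*Protocol article*

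**What the plan says.** The Objectives section of the Protocol article sets the economic aim: "The study will explore the potential impact of the psychological intervention on the cost to the Italian welfare system". On method it adds only this: "These assessments will be based on standard econometric indices", with QALYs and DALYs as examples.

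The Econometric assessment section gives the approach. Direct and indirect costs will be analysed, described as "costs of the management of COPD in our sample, referring to clinical notes and medical files". On health outcomes: "Changes in QoL and life expectancy data will be used to estimate QALYs", and DALYs likewise. The same sentence then names the comparison: "by comparing our data with international norms, we will gain insight into the sustainability and cost-efficiency of the psychological intervention".

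The design is stated in the abstract: "A two-arm randomised controlled trial will be conducted". The Proposed analyses section ties the treatment comparison to the "interaction between treatment (experimental versus control) and time (three repeated measures) on primary outcome variables", which it identifies as acceptance and adherence.

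**The concern.** The aim is incremental: what changes, in cost and in health, because patients receive psychological support. The stated comparison sets trial data against an external reference. A gap between the two can arise from who was enrolled, how ill they were, where and when they were treated and how care is priced, whether or not the support did anything.

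Followed as written, a favourable gap could be reported as cost-efficiency and an unfavourable one as its absence, with neither resting on the randomisation. This matters because the Discussion expects lower health care costs if the hypothesis is confirmed, so a reader will look for evidence of exactly that effect.

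**Working it through.** The article states no economic figure, so there is none to reproduce. The check is a reading of every place that could supply a between-arm economic contrast, followed by short algebra.

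**Reading**

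- *Objectives*: asks about the intervention's impact on cost and refers to standard indices. No comparator is named.
- *Econometric assessment*: costs are described for the sample as a whole. The one comparator named is external.
- *Proposed analyses*: the treatment-by-time interaction is for acceptance and adherence. The rest is descriptive summaries, within-group before-after tests and regression on baseline variables. None of these contrasts costs, QALYs or DALYs between arms.
- *Discussion*: mentions comparison with an active control group, but as protection against the Hawthorne effect and not for economic outcomes.

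**Algebra**

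Let E and C be mean QALYs in the experimental and control arms, and N the norm. Write e = E − C for the intervention effect and g = C − N for the gap that would exist without the intervention. Then

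E − N = (E − C) + (C − N) = e + g.

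The comparison with the norm equals the effect only if g = 0. Values of E − N for assumed e and g (none is in the article):

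| g | e = −0.05 | e = 0 | e = +0.05 |
|---|---|---|---|
| −0.20 | −0.25 | −0.20 | −0.15 |
| −0.10 | −0.15 | −0.10 | −0.05 |
| 0 | −0.05 | 0 | +0.05 |

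The value −0.15 appears under a harm of 0.05 and under a benefit of 0.05. So does −0.05. The observed difference therefore does not even fix the sign of the effect.

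If both arms are pooled, as the whole-sample wording for costs would allow, then with equal arms (E + C)/2 − N = g + e/2. For g = −0.10 and e = +0.05 this is −0.10 + 0.025 = −0.075: the gap remains in full and the effect is halved.

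If each arm is set against the same norm and the two differences are subtracted, (E − N) − (C − N) = e. The norm cancels, and what remains is the between-arm contrast that the article does not state.

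**Is g = 0 plausible?** The Subjects and setting section describes one Milan centre and patients with GOLD 2 to 3 disease for whom NIV is recommended. It excludes oncological history, most psychiatric disorders and stable antidepressant use. Nothing there suggests that untreated outcomes would match an international reference. The same algebra applies to costs, where g also carries differences in prices and in health system.

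**The case against.** **The arms may well be compared.** A reader might infer that norms replace the randomised comparison. The article does not say so. It is a two-arm trial, the aim is framed as the impact of the intervention, the analysis is by intention to treat, and the full protocol or an economic plan may exist elsewhere. This stands: a between-arm comparison is unstated, not excluded. What remains is that the article does name a comparator for cost-efficiency, and the one it names cannot do the job.

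**Norms may mean something else.** The phrase could refer to reference values for valuing QALYs and DALYs, or to a cost-per-QALY threshold. Its position just after the estimation of QALYs and DALYs makes this possible. But a threshold is applied to an incremental cost and an incremental QALY, and both still have to come from the arms.

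**The cost labels look more harmful than they are.** Hospitalisation for relapse is listed among "indirect (e.g. cost of hospitalisation for relapse, additional care, indirect social costs, etc.) costs". A reader might infer that the savings from fewer admissions would drop out of the result. The documents do not support this: both cost categories are to be analysed and no direct-only total is planned, so the label changes no overall total.

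**Psychologist time does not measure the error.** Four sessions of 30 min to eight of 45 min come to 120 to 360 min, or 2 to 6 h per patient. A reader might take that as the size of the problem. It says nothing about the bias of a comparison with norms, and it is not an incremental input, because controls also attend six sessions of about 30 min (180 min, or 3 h).

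**Detail left to a fuller plan.** How QALYs are computed, how deaths enter and how uncertainty is expressed are commonly left out of an article. Their absence is no part of this point.

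**Conclusion.** The point holds in limited form. The only comparison stated for cost-efficiency is with international norms, and it cannot answer the question set in the Objectives section, whichever way norms is read. The conclusion rests on the article's stated comparator and on the ordinary assumption that the untreated trial population need not equal the norm (g is not known to be 0).

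The size of the error cannot be derived from the document. The assumed values show only that it can exceed the effect and hide its sign. The consequence is confined to the economic conclusions: the aim is worded as exploratory, the article lists it as neither a primary nor a secondary outcome, and the conclusion on acceptance and adherence is unaffected.

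**What to change.** In the Econometric assessment section, replace the sentence on norms with a statement that:

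- incremental costs will be estimated between the randomised arms by intention to treat, counting all health-service costs, including hospitalisation, and the cost of delivering the sessions in both arms;
- incremental QALYs and DALYs will be estimated between the same arms;
- international norms will serve only as context, or as a decision threshold for the incremental result, with a note of which is meant.

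The cost is a short change of text and modest analysis work. EQ-5D is already planned at baseline and at 3, 6 and 12 months, and costs are already to be taken from clinical notes and medical files. The added need is to keep costs by patient and arm and to cost the sessions delivered in each arm. Sample size and primary analysis do not change.
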